**Fig. 1 Fig1:**
[figure not shown]
Flow chart of the PREP trial

### Blinding

Trial assistants and clinic nurses at each study center will be masked to the group allocation pre- and post-operatively. Due to the nature of the intervention, the patients cannot be blinded to the group allocation. In each center, two groups of physiotherapists will be assigned to the intervention group or the control group to maximally avoid performance bias. The trial administrators at each study center who are aware of the group allocation will assign patients in the intervention group to one medical unit whereas the control group to the other unit. The medical staff including assessors, surgeons, data analysts, and statisticians will be blinded to the group allocation.

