### Interventions

#### Control group

At their admission, patients in the control group will be provided with a color booklet containing information about the general procedure of lung cancer surgery, strategies of pain management, post-operative recovery process and potential complications, and the necessity and the importance of early ambulation and self-directed pulmonary rehabilitation to the post-operative recovery. Detailed written and pictorial instructions will direct the patients to correctly perform deep breathing and coughing. In this case, no verbal education or guided training will be provided by a physiotherapist.

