#### Exercise group

Apart from the booklet, patients in the exercise group will be provided with an additional 30-min training session guided by a physiotherapist. This session contains the verbal education and guided training of 1) diaphragmatic breathing, diaphragm muscles could be strengthened through this exercise (15 repetitions each set following 2-3 min rest for three sets). The patients inhale slowly to the maximum lung capacity through nose, and hold the breath for 2–3 s, then exhale slowly through tips with the abdominal muscles tighten; 2) effective coughing, the patient is requested to perform a slow-flow breath to maximum inspiratory capacity followed by a forced cough with the glottis opening. One hand of the patient or the physiotherapist presses over on the surgical region to support the wound and to encourage greater expiratory force; and 3) aerobic ambulation, the patient is encouraged to perform indoor walking and it is aiming for an initial intensity of 50–70% VO_2_ peak based on the results of 6MWT tested at the baseline with an increase of 10–15% VO_2_ peak per day according to the condition of each individual. They are requested to slow down or stop walking with the occurrence of chest tightness or breath shortness. Outside these assisted sessions, participants will be advised to walk or exercise by their bedside as frequently as they are able. Patients are requested to perform self-directed training till the operation day. After the surgery, a physiotherapist will assist the patients to walk as soon as possible on the first post-operative day. The diaphragmatic breathing, effective coughing and aerobic ambulation will be performed till the discharge day under the supervision of the physiotherapist to maximally avoid adverse events [32–34].

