### Sample size calculation

It has been reported that the absolute risk reduction in PPCs was of 20% by previous trials of preoperative education [45], and a post-operative PPC incidence of 32% was identified in patients with undergoing minimally invasive lung cancer surgery [2]. For the purposes of this trial, conservative goals (minimum 10% absolute risk reduction from a 20% baseline PPC risk) were set. A sample of 305 patients would have 80% power to detect a significant difference between groups (*p* = 0.05, two sided) with an 15% inflation to account for dropouts, non-compliance, and uncertainty of baseline risk, providing a final sample size of 500.

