### Statistical methods

Backward stepwise regression will be applied to select adjustment covariates from covariates which may have impact on the prognostic strength and effect sizes between groups. These covariates include: age, gender, BMI, smoking history, smoking index, pre-operative comorbidities and physical status, pre-operative hospital LOS, application of prophylactic antibiotics, surgical type, tumor location, length in time of operation, ICU admission immediately following the surgery, mode of post-operative analgesia, type of lung cancer according to the intra- or post-operative pathological examination, time in day and type of post-operative antibiotic delivery, post-operative analgesia management, and postoperative daily drainage [46, 47].

For all outcomes we estimated differences in effect size between groups on an intention-to-treat basis. Multivariate robust random or mixed effects Poisson regression will be applied to estimate primary outcome efficacy and binomial secondary outcomes (cardiopulmonary complications and other complications). The time effect of day the PPC diagnosed between groups will be estimated with Cox proportional hazards regression with or without adjustment for covariates. Secondary outcomes with normal and abnormal distributions, including cardiopulmonary endurance, muscle strength, activity level, HRQoL, time in day of the application of antibiotics, pre- and post-operative hospital LOS and total hospital LOS, will be estimated for group differences with mixed effects ordered logistic regression and mixed effects linear regression.

Exploratory post hoc sensitivity adjusted analyses will be performed to determine the effect of specific covariates (discrepancy in experience grade of treating physiotherapist, hospital level, surgical category, tumor location, preoperative respiratory complication risk score, age and gender) across all primary and major secondary outcomes [48].

All analyses will be performed using Stata version 16 or later (StataCorp, College Station, TX, USA).

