The PREP trial is the first multicenter RCT designed to investigate whether pulmonary rehabilitation based ERAS program reduces the incidence of PPCs, and improves pulmonary function and HRQoL following lung cancer surgery. It has been widely recognized that a well-designed and powered multicenter RCT can provide the highest level of evidence to prove the effectiveness of certain interventions. However, performing a multicenter RCT may be with great difficulties. For example, the standardized intervention needs to be delivered across all the participating centers and the trial period. This can be addressed to train the physiotherapists in advance. The standard operation procedure (SOP) booklet and standard operation video have been drafted and recorded respectively. The physiotherapists from all the participating centers are required to adhere to the instruction as included within the SOP booklet and the digital video recording. Considering the discrepancy of learning curve and knowledge background across senior and junior physiotherapists, experience varies between participating centers, and will vary over time. We have not attempted to standardize these due to the feasibility of doing so across the six participating centers. Instead, the impact of potential confounders can be pooled and adjusted during statistical analysis. In addition, patient-oriented confounders, including timing of post-operative ambulation, pre-operative hospital LOS or post-operative analgesia management, have not been strictly controlled since this would be extremely difficult to achieve. Nonetheless, we believe that with effective randomization and blinding, it is reasonable to expect that patients in both groups will have an equal chance of exposure to these factors. Moreover, the differences in effect sizes of PREP versus control on all outcomes will be estimated with the intention-to-treat based different regression analysis which may be a complementary way to study new interventions rather than relying on simple Independent sample t-test or One-way ANOVA [18]. In similar with the placebo in the pharmaceutical research, the control group will be provided with educational booklet instead of no-intervention comparator. This action would be helpful to control for the Hawthorne effect and smooth the conduct of the PREP trial.

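### Physiotherapists are nested in the exercise arm, but the plan names no therapist level for the primary model; if therapists' results differ, the interval for PREP will be too narrow

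*Protocol article*

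**What the plan says.** **Delivery.** Under Blinding, the protocol article states: "In each center, two groups of physiotherapists will be assigned to the intervention group or the control group to maximally avoid performance bias". Under Exercise group, "patients in the exercise group will be provided with an additional 30-min training session guided by a physiotherapist", and physiotherapist supervision continues after surgery until discharge. Under Control group, "no verbal education or guided training will be provided by a physiotherapist".

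**Variation between therapists.** The Discussion describes advance training, a procedure booklet and a video that all physiotherapists must follow. On differences between senior and junior staff it adds: "experience varies between participating centers, and will vary over time. We have not attempted to standardize these". It leaves such differences to be dealt with in the analysis.

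**Analysis.** Under Statistical methods, "Multivariate robust random or mixed effects Poisson regression will be applied to estimate primary outcome efficacy and binomial secondary outcomes". The text does not say what the random effect or the robust variance is grouped on. Therapist appears once, as the experience grade of the physiotherapist treating the patient, among the covariates for exploratory post hoc sensitivity analyses. It is not among the candidate covariates for the main model. The Sample size calculation contains no allowance for clustering.

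**The concern.** This is a partially nested design. Patients are randomised individually, but exercise patients then share therapists and controls do not receive the therapist-delivered treatment. Randomisation cannot balance therapist, because the exercise-arm therapists treat that arm alone. If some obtain better results than others, outcomes of patients with the same therapist are correlated, and the variance of the exercise-arm rate has a between-therapist part.

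The one therapist term that the plan names does not deal with this. A grade covariate shifts the mean for senior against junior staff; two therapists of the same grade can still differ, and their patients remain correlated. A random intercept for centre does not deal with it either, because it moves both arms of a centre together while the therapist effect acts in one.

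At stake are the width of the interval and the size of the test for the primary outcome, and likewise for functional outcomes that depend on coaching. The conclusion would also apply less clearly to therapists other than those in the trial.

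**Working it through.** **The plan's own figure.** The inputs are "conservative goals (minimum 10% absolute risk reduction from a 20% baseline PPC risk) were set", a significance level of "0.05, two sided", and "A sample of 305 patients would have 80% power to detect a significant difference between groups". The standard two-proportion formula gives 199 per arm, 398 in total (438 with continuity correction), so 305 is not reproduced. With 1:1 allocation, power is 69% at 305 in total and 88% at 500. That mismatch is a separate matter. Here only the 500 (about 250 per arm) and the rates are used, and no ICC or design effect enters the plan's figure.

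**Assumptions, none given in the article.** 2, 3 or 5 exercise-arm therapists in each of the 6 centres (K = 12, 18 or 30); equal caseloads; one therapist per patient; ICC 0.01, 0.02 or 0.05; equal true risk in both arms for the type I error.

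**Formulas, for an analysis that ignores therapist.**
- Patients per therapist: m = 250/K.
- Design effect in the exercise arm: DE = 1 + (m − 1) × ICC.
- Variance ratio of the difference under the null: V = (1 + DE)/2, since only one of two equal arms is clustered.
- Actual type I error: 2 × [1 − Φ(1.96/√V)].

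**Worked case, K = 12, ICC 0.05.** m = 20.83; DE = 1 + 19.83 × 0.05 = 1.99; V = 1.496; √V = 1.223; 1.96/1.223 = 1.60; type I error 10.9%.

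| Therapists | m | ICC 0.01 | ICC 0.02 | ICC 0.05 |
|---|---|---|---|---|
| 12 | 20.8 | 6.2% | 7.3% | 10.9% |
| 18 | 13.9 | 5.7% | 6.5% | 8.8% |
| 30 | 8.3 | 5.4% | 5.9% | 7.2% |

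At ICC 0 every entry is 5.0%. One therapist per centre (K = 6) lies outside the assumed range and would give 7.4%, 9.8% and 16.8%.

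**Check by simulation.** With 20,000 runs, 252 per arm, beta-binomial therapist effects in the exercise arm and a common 15% risk, an analysis ignoring therapist gave 5.6%, 6.9% and 10.7% for K = 12, in line with the first row.

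**Effect at 20% against 10%.** The correct interval is wider by the factor √[(0.16 + 0.09 × DE)/0.25]. For DE = 1.07 (K = 30, ICC 0.01) this is 1.013; for DE = 1.99 it is 1.165. Power with 500 analysed and a correct standard error, using the pooled null variance times V, falls from 88% to 87% and 74% respectively.

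**What the open choice of grouping does.** In the same simulation, over 6 to 18 therapists and ICC 0 to 0.05:
- Robust variance grouped on therapist, normal reference: 5.0% to 8.1%.
- The same with a t reference on K − 1 degrees of freedom: 1.7% to 3.9%, which over-corrects.
- Robust variance grouped on centre, t reference on 5 degrees of freedom: 4.4% to 5.0%.
- Grouped on centre, normal reference: about 10% at every ICC including 0. That reflects having only six clusters and is not a therapist effect.

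**The case against.** The strongest reply is that the article plans random or mixed effects with robust errors, which are tools for dependent data, and that naming the level is ordinary content of an analysis plan that is not shown. That stands in part. A reader might infer that the plan treats patients as independent; the text does not say so. One reading that the wording allows, robust variance grouped on centre with a t reference, shows no excess error. But the article does not leave therapist differences wholly to another document. It relies on the analysis to handle them and names a method, the post hoc grade covariate, that cannot correct the standard error.

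Other stronger readings are also unsupported:
- That each patient is treated by one of a few therapists. Neither the number of therapists nor continuity of care is given. If staff share patients, the design-effect formula does not apply as used.
- That skill is left unstandardised. Experience is; technique is governed by training, booklet and video, which should lower the ICC.
- That type I error certainly exceeds 5%. If the programme affects no patient and therapists therefore do not differ, it is 5%. Interval coverage when PREP does work is the firmer worry.
- That therapist identity is not collected. The Data collection section does not list it, but the case report form is not shown, and the planned grade analysis needs at least the grade.

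Finally, the control arm also has an assigned physiotherapist group and its own medical unit, so independence of controls is not assured. That is true, but controls are not given the therapist-led component.

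**Conclusion.** The point holds conditionally. The text supports nesting of therapists in the exercise arm, admitted differences in experience, and a stated remedy that does not address correlation within therapist. No grouping level covering therapist is named for the primary model. If therapists' outcomes differ and the fitted model has no therapist level or other grouping that absorbs it, type I error would be about 5.4% to 10.9% and the correct interval about 1% to 16% wider at the design rates, under 12 to 30 therapists and an ICC of 0.01 to 0.05. Both ranges are assumptions. The low end is negligible; the high end needs two therapists per centre and the largest ICC considered. The change is worth making because it is cheap, because the trial is enrolling, and because therapist identity may be hard to recover later if it is not being recorded.

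**What to change.** 1. Record on the case report form, for each exercise patient, the study ID of the main treating physiotherapist, defined as the one who gives the pre-operative session, with a flag for shared care.
2. Name the grouping levels of the primary model. As the primary specification, or at minimum as a prespecified sensitivity analysis of the primary outcome, add a therapist-within-centre random effect acting in the exercise arm only, on top of centre.
3. Prespecify a small-sample correction. A therapist-grouped robust variance with a normal reference reached 8.1% in the simulation, and a t reference on K − 1 degrees of freedom was too conservative, so check the chosen correction by simulation once therapist numbers are known.
4. Report the therapist ICC, and keep the experience-grade analysis exploratory.

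The cost is one form field, a few lines of code and a slightly wider interval; no extra patients or staff. The change does not address the separate placement of each arm in its own medical unit within a centre, which a therapist random effect cannot remove.

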### Interventions

#### Control group

At their admission, patients in the control group will be provided with a color booklet containing information about the general procedure of lung cancer surgery, strategies of pain management, post-operative recovery process and potential complications, and the necessity and the importance of early ambulation and self-directed pulmonary rehabilitation to the post-operative recovery. Detailed written and pictorial instructions will direct the patients to correctly perform deep breathing and coughing. In this case, no verbal education or guided training will be provided by a physiotherapist.

#### Exercise group

Apart from the booklet, patients in the exercise group will be provided with an additional 30-min training session guided by a physiotherapist. This session contains the verbal education and guided training of 1) diaphragmatic breathing, diaphragm muscles could be strengthened through this exercise (15 repetitions each set following 2-3 min rest for three sets). The patients inhale slowly to the maximum lung capacity through nose, and hold the breath for 2–3 s, then exhale slowly through tips with the abdominal muscles tighten; 2) effective coughing, the patient is requested to perform a slow-flow breath to maximum inspiratory capacity followed by a forced cough with the glottis opening. One hand of the patient or the physiotherapist presses over on the surgical region to support the wound and to encourage greater expiratory force; and 3) aerobic ambulation, the patient is encouraged to perform indoor walking and it is aiming for an initial intensity of 50–70% VO_2_ peak based on the results of 6MWT tested at the baseline with an increase of 10–15% VO_2_ peak per day according to the condition of each individual. They are requested to slow down or stop walking with the occurrence of chest tightness or breath shortness. Outside these assisted sessions, participants will be advised to walk or exercise by their bedside as frequently as they are able. Patients are requested to perform self-directed training till the operation day. After the surgery, a physiotherapist will assist the patients to walk as soon as possible on the first post-operative day. The diaphragmatic breathing, effective coughing and aerobic ambulation will be performed till the discharge day under the supervision of the physiotherapist to maximally avoid adverse events [32–34].

### Withdrawal from trial

Patients will be withdrawn for either of the following: (i) the patient makes such a request; (ii) the patient develops a serious disease, such as heart disease or stroke, and continuing their participation becomes inappropriate in the opinion of the investigators; (iii) an severe adverse event related to the pulmonary rehabilitation program occurs or (iv) with poor compliance to the training protocol.

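### Withdrawal reasons (iii) and (iv) act on the exercise arm alone and conflict with the intention-to-treat analysis unless withdrawal means only that training stops, which the article does not say

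*Protocol article*

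**What the plan says.** The section Withdrawal from trial in the protocol article opens with "Patients will be withdrawn for either of the following" and lists four reasons: (i) the patient's request; (ii) serious disease, where "continuing their participation becomes inappropriate in the opinion of the investigators"; then (iii) and (iv), which read "an severe adverse event related to the pulmonary rehabilitation program occurs or (iv) with poor compliance to the training protocol".

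The arms differ in what they could fail to comply with or be harmed by. Under Exercise group, "patients in the exercise group will be provided with an additional 30-min training session guided by a physiotherapist", followed by self-directed practice up to surgery and supervised training from the first day after surgery until discharge. Under Control group, patients receive a booklet, and "no verbal education or guided training will be provided by a physiotherapist".

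On analysis, Statistical methods states "For all outcomes we estimated differences in effect size between groups on an intention-to-treat basis". The Discussion repeats the intention-to-treat commitment.

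Nothing in the article says that a patient withdrawn under (iii) or (iv) remains under PPC assessment to Day 14 or attends the 2- and 12-week follow-ups.

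**The concern.** A control patient cannot have an adverse event related to a programme that the control arm does not receive, and has no supervised sessions against which compliance could be judged. Followed as written, reasons (iii) and (iv) therefore filter one randomised group on what happens after randomisation.

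The filter may also track the primary outcome. Supervised training runs to discharge, and so overlaps the 14-day window for PPCs. The Exercise group section tells patients to slow down or stop walking if the chest feels tight or they become breathless. Someone developing a PPC may thus train poorly and meet reason (iv), which has no threshold and will be judged largely on reports from patients and physiotherapists who know the allocation. Blinded outcome assessors cannot correct for patients who have already left.

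Intention-to-treat needs outcomes from poor compliers. If they are not collected, no analysis plan can restore them, and the loss would tend to favour the programme.

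**Working it through.** **Step 1: the text.** The plan gives no figure for withdrawals under (iii) or (iv), so there is none to reproduce. The point rests on setting sections side by side.

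- Withdrawal from trial: removal is mandatory, the heading refers to the trial, and reason (ii) speaks of participation. This is the language of leaving the study.
- Control group and Exercise group: the programme and the guided training exist in one arm only.
- Statistical methods: all outcomes are to be compared by intention-to-treat.
- Sample size calculation: non-compliance is grouped with dropout in one 15% inflation. This is consistent with treating non-compliers as lost, but does not prove it.

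These fit together only if withdrawal means that training ends and follow-up does not.

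**Step 2: how large a bias could be.** Inputs from the article: 20% baseline PPC risk, a 10-point target reduction, and 500 patients allocated about equally, so 500/2 = 250 per arm. Assumptions not in the article: there is no true effect; a share *w* of the exercise arm is withdrawn under (iii)–(iv) and contributes no PPC data; those patients have *r* times the PPC risk of the patients who stay; the control arm is complete.

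The exercise arm's risk is 0.20 = (1 − w)p + w·r·p, where p is the risk among those who stay. Hence p = 0.20/(1 − w + w·r), and the spurious reduction is d = 0.20 − p.

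| w | r | p | d (points) | Apparent risk ratio | Two-sided error |
|---|---|---|---|---|---|
| any of 5%, 10%, 15% | 1 | 0.200 | 0 | 1.00 | 5.0% |
| 5% | 2 | 0.20/1.05 = 0.190 | 1.0 | 0.95 | 5.8% |
| 10% | 2 | 0.20/1.10 = 0.182 | 1.8 | 0.91 | 7.9% |
| 15% | 2 | 0.20/1.15 = 0.174 | 2.6 | 0.87 | 10.9% |
| 15% | 3 | 0.20/1.30 = 0.154 | 4.6 | 0.77 | 25.0% |

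The last column is the chance of a nominally significant result when there is no effect, from a normal-approximation test of two proportions with 250 controls and 250(1 − w) exercise patients. It equals P(Z > (1.96·se0 − d)/se1) + P(Z < (−1.96·se0 − d)/se1), with se0 the pooled and se1 the unpooled standard error.

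Example, w = 15%, r = 2: n = 250 and 212.5; d = 0.0261; pooled risk = (50 + 36.96)/462.5 = 0.188; se0 = 0.0365; se1 = 0.0363. The upper tail is 10.6% and the lower tail 0.4%, together 10.9% before rounding of the parts.

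If every randomised patient is followed and analysed, d = 0 and the error is 5.0% whatever w and r are.

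**The case against.** A reader might infer more than the article supports.

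*That withdrawn patients are excluded from the analysis.* No sentence says so, or says that data collection stops. An article condenses a fuller protocol, and analysis sets and follow-up after withdrawal are often left to that document or to the analysis plan. This stands: the loss of data is inferred. What remains is a stated, mandatory, one-arm rule that clashes with a stated analysis principle. That is not missing detail.

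*That control patients also have a training protocol.* The booklet does give exercises: "Detailed written and pictorial instructions will direct the patients to correctly perform deep breathing and coughing". But this is self-directed and no monitoring of it is described, so guided training in the exercise arm is the natural meaning of reason (iv).

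*That reason (ii) deletes cardiac outcomes.* It covers the case where "the patient develops a serious disease, such as heart disease or stroke", while heart failure and arrhythmia are secondary outcomes. But reason (ii) applies to both arms, also needs the investigators' judgement, and is triggered by an event already observed. Only later outcomes could be lost. It does not support a one-arm bias.

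*That harm is understated.* Under (iii) the severe event is itself the trigger, so it is known before the patient leaves. The Data monitoring section has the safety committee review both safety and withdrawals. The documents do not support this charge.

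*That the bias is near half the target effect.* The 4.6-point figure is the top corner of an assumed range. Its 15% share equals the plan's whole allowance for dropout, non-compliance and uncertain baseline risk, here placed on two reasons in one arm. Supervision of training and daily PPC assessment may keep true losses smaller. If those withdrawn were at lower risk, the sign would reverse.

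**Conclusion.** The point holds for reasons (iii) and (iv). As written they remove patients from the exercise arm only, after randomisation, and this conflicts with the intention-to-treat commitment unless withdrawal means no more than stopping training.

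Any bias in the primary result depends on two conditions that the article does not settle: that these patients are lost to PPC assessment, and that their risk is higher. If both hold, the bias favours the programme. Over the cases tabulated it runs from 0 to 4.6 points against the 10-point target, and the more moderate 2-fold cases give 1.0 to 2.6 points. The withdrawn share and the risk ratio are assumed throughout. The textual conflict itself rests on no assumption and should be resolved while the trial is enrolling, because outcomes not collected by the end of follow-up cannot be reliably recovered.

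**What to change.** Reconcile Withdrawal from trial with Statistical methods by separating two things: stopping the training, and ending data collection.

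- Remove poor compliance as a reason for withdrawal from the trial and record it as adherence.
- State that, unless consent is withdrawn, PPC ascertainment to Day 14 and the scheduled outcome collection continue as far as feasible after training stops.
- State that every patient is analysed in the arm to which they were randomised.
- For anyone already withdrawn under (iii) or (iv), seek the outcome data, subject to consent.

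When training or physical tests should stop, including under reason (ii), stays with the investigators. The change concerns data collection only.

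The cost is a short amendment with a note to sites, and follow-up of some further patients at visits already scheduled. Under the assumed 5% to 15% of 250, that is about 13 to 38 patients. Recovering outcomes from patients already withdrawn may need ethics or consent steps. Keeping poor compliers dilutes the estimate somewhat, which is the price of the intention-to-treat comparison that the plan has chosen.
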